## **6 RANDOMIZATION AND MASKING PROCEDURES**

The study is not randomized or masked.

## 7 STUDY TREATMENTS

### 7.1 Investigational Drug and Device Specifications

< *QLT091001 description redacted* >

### 7.2 Drug Dosage and Administration

The administration of study treatment was staggered by at least 48 hours between the first and second subjects in the study. (This was completed already at the Canadian study center.)

The dose of 40 mg/m^2 QLT091001 will be administered in this study. This was the highest dose evaluated in a study of healthy adult volunteers (Study RET HV 01).

Dosing will be based on each subject's body surface area (BSA). Each subject's BSA will be calculated using the following formula:

$$\text{BSA (m}^2\text{)} = ( [\text{Height(cm)} \times \text{Weight(kg)} ] / 3600 )^{1/2} \quad \text{e.g. BSA} = \text{SQRT}( (\text{cm*kg})/3600 ).$$

Subjects will have height and weight measured twice (for verification) before dosing, as indicated in [Section 9.1 \(Table 3\)](#). A second qualified person will verify the BSA calculation, the dosing calculation, and preparation of the dose.

Refer to the RET IRD 01 Procedure Manual for complete details regarding dosing calculations.

QLT091001 should be dispensed while wearing gloves using syringes in a room with low lighting.

Subjects will receive 7 consecutive oral loading doses, administered once daily in the morning within 10 minutes after breakfast from Days 0 to Day 6 (inclusive).

Diet and exercise (as well as smoking and drinking) will be restricted. See [Section 9.8](#) for complete details regarding these restrictions.

### **7.3 Drug Dose Modification**

The drug dose may be reduced for a given subject if the proposed dose is poorly tolerated in the clinical Investigator's judgment. Tolerance will be evaluated by monitoring clinical laboratory tests and AEs as defined in the study schedule of events ([Section 9.1](#)).

### **7.4 Concomitant Treatment**

Study subjects are not permitted any medications during the treatment period of the study and for 7 days post-treatment, except hormonal contraceptives or if required to manage an adverse event or an ongoing medical issue not precluded by exclusion criteria (Section 5.3). For example, asthma is not precluded by exclusion criteria, so subjects with asthma may enter the study and may need medication during the study; such medication is permitted. As much as possible, such medication should remain at the same dose during the treatment period and for 7 days post-treatment. Any concomitant medications given during the study must be recorded on the CRF and in the source document, including start and stop dates, route, and indication.

Treatment procedures, such as surgical procedures, must be recorded on the CRF and in the source document including start and stop dates. Surgical anesthetics, paramedical or alternative therapies (i.e., acupuncture, massage) should not be recorded on the CRF.

## **8 RISKS/PRECAUTIONS**

The risks of QLT091001 in humans are not known, but may be estimated based on the pharmacological class and observed effects in animal toxicology studies and a recent dosage escalation study in normal human controls.

As a precaution against any unanticipated, severe risk to the administration of QLT091001, the treatment will be administered in a medical facility, with immediate access to equipment and staff for resuscitating and stabilizing individuals in an acute emergency (such as cardiac emergencies, anaphylaxis, cytokine release syndrome, convulsions, hypotension), and in reasonable proximity to Intensive Care Unit facilities.

See [Section 1.5](#) and [Section 1.6](#) for further details about the study conducted in healthy volunteers.

## 8.1 Signs and Symptoms of Hypervitaminosis A

An overdose of QLT091001 may be expected to present with signs and symptoms similar to chronic vitamin A toxicity (hypervitaminosis A syndrome). Table 2 lists the clinical signs and symptoms that have been reported in subjects with chronic vitamin A toxicity.

**TABLE 2. Signs/Symptoms of Hypervitaminosis A Syndrome**

| Body System            | Effects                                                                                                                                                                                             |
|------------------------|-----------------------------------------------------------------------------------------------------------------------------------------------------------------------------------------------------|
| Mucocutaneous          | Dry skin, desquamating rash, pruritus, cheilitis, epistaxis, hair loss, gingivitis, skin fragility and easy bruising, edema, ingrown nails                                                          |
| Ophthalmologic         | Blepharitis, papilledema, exophthalmos, diplopia, nystagmus, blurred vision                                                                                                                         |
| Neurologic/Psychiatric | Pseudotumor cerebri, headache, depression, psychosis, irritability, fatigue, daytime hypersomnolence, insomnia, lethargy, mood changes                                                              |
| Gastrointestinal       | Nausea, vomiting, abdominal pain, anorexia, weight loss, hepatomegaly, splenomegaly, hepatitis, cirrhosis, ascites, varices, hyperlipidemia, elevated liver function tests and alkaline phosphatase |
| Skeletomuscular        | Muscle soreness and stiffness, arthralgia, bone pain, periosteal thickening/calcification, premature closure of epiphyses in children, growth retardation, ossification                             |
| Endocrine              | Polyuria, polydipsia, abnormal thermoregulation (cold extremities, fever, chills, night sweats)                                                                                                     |
| Other                  | Elevated prothrombin time (due to vitamin A inhibition of vitamin K absorption), teratogenicity                                                                                                     |

Source: [39]

The vitamin A doses that are associated with chronic toxicity in a given individual can vary greatly, but generally, doses that exceed normal dietary intake by 15,000 IU/day—or 5 times the recommended daily amounts of 700 µg/day for women and 900 µg/day in men [49]—over several months to years are potentially associated with hypervitaminosis A [39]. Signs and symptoms of hypervitaminosis A typically resolve without long-term sequelae within 2-8 weeks of discontinuing supplementation. However, the reversibility of hepatic or bone effects is less predictable, with some subjects continuing to display abnormal liver function tests or cirrhosis. Teratogenic effects, of course, are also a permanent consequence of vitamin A toxicity.

## 8.2 Anticipated Clinical Effects Based on Nonclinical Studies

The NOAEL in a monkey toxicology study with 28 days of dosing was 5 mg/kg or 60 mg/m^2 (most relevant species for comparison to humans). Findings at this dose were limited to changes in liver function tests that were not considered clinically significant, did not lead to any changes in treatment, and were reversible after the 28-day treatment course was completed [50].

The target organs for toxicity at the doses above the NOAEL in nonclinical studies were:

- Liver – potential effects will be monitored in this study with serum concentrations of liver enzymes and lipids.

- Bone – potential effects will be monitored in this study by monitoring serum concentrations of alkaline phosphatase and inorganic phosphate. Adverse effects on bone are considered unlikely given the short exposure period in this study.
- Heart – potential cardiac effects will be monitored in this study with ECG and vital signs.

### 8.3 Anticipated Clinical Effects Based on Clinical Studies

See [Section 1.5](#) for a description of results from the RET HV 01 study. In the current ongoing study (RET IRD 01), preliminary safety data from a total of 14 subjects treated with QLT091001 (12 received 40 mg/m^2 and 2 received 10 mg/m^2) was assessed. In these studies, adverse effects included the following, which may be potential risks with the study drug:

- GI Disorders: nausea
- General Disorders and Administration Site Conditions: asthenia, facial flushing
- Metabolism and Nutrition Disorders: decreased appetite
- Nervous System Disorders: facial burning sensation, headache, photophobia, dizziness
- Investigations: hemoglobin decreased, RBC count decreased, increased triglycerides, decreased HDL, increased or decreased LDL, increased cholesterol, increased AST

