### **1.5 Study RET HV 01 (Safety, First in Humans)**

Study RET HV 01 was conducted to investigate the safety and tolerability of daily oral doses of QLT091001 for 7 days in 6 dose level cohorts of healthy adult volunteers. Three subjects were included in each dose cohort with the exception of the highest dose cohort which included 5 subjects. Doses escalating from 1.25 mg/m^2 to 40 mg/m^2 were tested in series approximately 2-3 weeks apart through a doubling process (1.25 to 2.5 to 5.0 to 10 mg/m^2 etc.). For each dose cohort, extensive laboratory tests and vital signs were evaluated at Screening, the evening before dosing, the next morning shortly before the initial dose, and at regular intervals during and after the 7-day dosing period. AEs were evaluated at every visit beginning on Day 1. Holter monitoring was done at Screening, 24 hours following the first dose, and the day after the last dose; ECGs were done at Screening, the day before the initial dose, before and after dose 3, and 3 days after the last dose. When all test results up to 3 days after the seventh dose were available for a specific cohort, a safety monitoring committee reviewed the information before dose escalation was allowed for the next cohort.

In the cohorts dosed with 10 to 40 mg/m^2, a reduction of plasma high density lipoprotein (HDL) concentrations was observed in most subjects. This HDL reduction did not appear to be dose-dependent and was rarely out of the normal-low range. Some of these subjects also had milder reductions of plasma low density lipoprotein (LDL) concentrations. Isolated reductions in one or more hematologic parameters (hemoglobin, red blood cells, hematocrit) were also noted in 2 subjects (1 subject who took the 5 mg/m^2 dose and 1 who took the 40 mg/m^2 dose) but these events were mild and not considered to be clinically significant. Drug-related adverse symptoms only occurred in the 5 subjects receiving 40 mg/m^2 who all

reported mild headache(s); some subjects also reported mild facial flushing (2/5) and mild loss of appetite (2/5) and 1 subject reported moderate nausea. These AEs were noted during the first 4 days of dosing and resolved thereafter.

Overall, 7 daily oral doses of QLT091001 up to 40 mg/m^2 were well tolerated. A more complete description of this study is provided in the Investigator Brochure (IB).

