### **4 INVESTIGATIONAL PLAN**

#### **4.1 Overall Study Design**

This will be an open-label, proof-of-concept, phase 1b study. The study will include up to 28 subjects with LCA or RP due to inherited deficiency of *RPE65* or *LRAT* (up to 14 subjects for each disease cohort). Subjects in each disease cohort (including 2 gene mutation subgroups) will receive a once-daily oral loading dose of 40 mg/m^2 QLT091001 for 7 consecutive days, which was the maximum dose assessed in study RET HV 01 (see Figure 4). Subjects with either LCA or RP will be enrolled at 1 study center in Canada. A maximum of 5 subjects with RP will be enrolled at 2-3 study centers in the US. Adult subjects with RP will be enrolled at approximately 3 study centers in the EU.

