### 11.4.1 Best-Corrected Visual Acuity Using ETDRS Testing

Visual acuity scores based on ETDRS testing and changes from baseline will be provided for each time point by gene mutation subgroup and disease cohort using descriptive statistics (mean, standard deviation, minimum, median, and maximum).

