### **11.5 Safety Variables and Analyses**

Safety analyses will be performed on all subjects who received treatment (safety data set). This study has the following safety variables:

- Adverse events (AEs)
- Concomitant medications
- Vital signs (temperature, blood pressure, heart rate, respiratory rate)
- Clinical laboratory tests (including hematology, chemistry, urinalysis, thyroid function, serum retinol, and coagulation testing)
- Electrocardiogram (ECG) measurements
- Height
- Biomicroscopy, IOP, and dilated fundus exam
- BCVA score

AEs will be coded using the Medical Dictionary for Regulatory Activities (MedDRA) with the number and percentage of subjects experiencing an AE and the total number of events summarized with system organ class and preferred term. Concomitant medications will be coded with the World Health Organization Drug Dictionary (WHO DD) and tabulated. Other safety variables including clinical laboratory test results and vital signs will be summarized with appropriate descriptive statistics. ECG, biomicroscopy, IOP, dilated fundus exam, and cycloplegic refraction results will be listed by subject. See [Section 9.5](#) for details on the visual acuity score.

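### Two of 14 treated subjects are recorded at 10 mg/m2 in a study described as single-dose 40 mg/m2, and the stated summaries do not separate dose

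*Protocol*

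**What the plan says.** **Planned dose.** Protocol 4.1 states that subjects in each disease cohort, including both gene subgroups, "will receive a once-daily oral loading dose of 40 mg/m 2 QLT091001 for 7 consecutive days". Section 7.2 repeats it: "The dose of 40 mg/m 2 QLT091001 will be administered in this study". The Protocol Summary names the same single dose.

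**Permitted reduction.** Section 7.3 provides that "The drug dose may be reduced for a given subject if the proposed dose is poorly tolerated", in the investigator's judgment. Section 2.2 says much the same. Neither names a reduced level.

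**Dose received.** Section 8.3 begins "In the current ongoing study (RET IRD 01), preliminary safety data from a total of 14 subjects treated with QLT091001" and breaks the 14 down as "12 received 40 mg/m 2 and 2 received 10 mg/m 2". No section describes a 10 mg/m2 group or ties these two subjects to the reduction rule.

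**Analysis sets and groupings.** The ITT set is all enrolled subjects (11.2.1) and the safety set is all treated subjects (11.2.2). Visual acuity is summarized "for each time point by gene mutation subgroup and disease cohort" (11.4.1). ERG (11.4.2), the other efficacy variables (11.4.4) and the questionnaire (11.6.1) use gene subgroup and disease cohort. Goldmann visual field is summarized for all subjects together (11.4.3). Adverse events are reported as "the number and percentage of subjects experiencing an AE", by system organ class and preferred term (11.5). None of these summaries mentions dose.

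**The concern.** The design sections and 8.3 give different accounts of what subjects in this study received. The two doses differ fourfold (40/10), and the protocol's own background gives reason to think dose matters:

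- In the healthy-volunteer study, "Drug-related adverse symptoms only occurred in the 5 subjects receiving 40 mg/m 2" (1.5).
- In the mouse study behind the dose rationale (2.2), 3 mg/m2/day gave a small ERG effect and 12 and 37.5 mg/m2/day a stronger one. Retinal 9-*cis* compounds were detected only at those two higher doses; 10 mg/m2 lies below both.
- The notes to 2.2 raise the possibility that LRAT subjects need a higher dose to respond. If both 10 mg/m2 subjects were in one gene subgroup, a comparison of the gene subgroups would mix genotype with dose.

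At stake is what the summaries describe. A mean change or an adverse event percentage over all subjects is a mixture of doses, in groups small enough for two subjects to move it. Goldmann visual field, which 4.2.1 puts forward as a possible primary endpoint for later trials, has the broadest pooling.

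**Working it through.** **Inputs**

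- 14 treated subjects in the preliminary data: 12 at 40 mg/m2 and 2 at 10 mg/m2 (8.3).
- Up to 28 subjects, 14 per disease cohort, 7 per genotype within disease cohort (4.1, 5.1, 11.1).
- Effect at 10 mg/m2: not given. Let f be that effect as a fraction of the effect at 40 mg/m2, with an assumed range of 0 to 1.

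**The plan's own figures**

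- 12 + 2 = 14, as 8.3 states.
- 2 diseases × 2 genes × 7 = 28, as 11.1 states. There is no power calculation to reproduce; the sample size rests on rarity and clinical judgment.

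**Share of each group at 10 mg/m2** (2/n)

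- Of 28: 2/28 = 7.1%.
- Of 14: 2/14 = 14.3%. This applies to the 14 treated, or to a full disease cohort holding both subjects.
- Of a 7-subject cell holding both: 2/7 = 28.6%.

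**Pooled mean change relative to the 40 mg/m2 mean.** With two subjects at 10 mg/m2 among n, the ratio is (n − 2 + 2f)/n.

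| n | f = 0 | f = 0.25 | f = 0.5 | f = 1 |
|---|---|---|---|---|
| 28 | 26/28 = 0.93 | 0.95 | 0.96 | 1.00 |
| 14 | 12/14 = 0.86 | 0.89 | 0.93 | 1.00 |
| 7 | 5/7 = 0.71 | 0.79 | 0.86 | 1.00 |

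The last row applies only if both subjects are in the same gene-by-disease cell. The first row assumes that no one beyond these two receives a lower dose.

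**Adverse events.** No gene-by-disease grouping is stated for them, so the relevant denominator is all treated subjects. As an extreme illustration, a symptom present in every subject at 40 mg/m2 and in none at 10 mg/m2 would appear as 12/14 = 86% in the preliminary data. With 28 treated and only these two at 10 mg/m2, it would appear as 26/28 = 93%.

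The evidence for such a contrast is thin. The healthy-volunteer cohort at 10 mg/m2 had 3 subjects (1.5), and 0 of 3 has a one-sided 95% upper bound of 1 − 0.05^(1/3) = 63%.

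**The case against.** The strongest reply is that displaying two off-dose subjects is detail for a statistical analysis plan, which is not at hand, and that no sentence in the protocol says doses will be pooled. This stands in part: an analysis plan could add a split. But the protocol does fix its data sets and its groupings, and following them puts both doses in the same groups. The text also already knew that two doses had been given.

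A second reply is that 2.2 and 7.3 allow lower doses, so 10 mg/m2 need not depart from the protocol. That is fair; the two subjects may be permitted reductions. The document does not say, and either way they go unseparated in the summaries.

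Third, this is an uncontrolled, descriptive phase 1b study with no stated test or primary endpoint, so no error rate depends on these means. That stands and limits the seriousness.

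Several stronger readings are tempting but unsupported:

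- A reader might take 71% or 86% as the expected dilution. Those values need f = 0, whereas 2.2 places 10 mg/m2 inside the expected active range of 3 to 37.5 mg/m2/day. The 71% also needs both subjects in one cell, and neither their cohort nor their genotype is given.
- A reader might conclude that adverse event incidence is understated. The volunteer data suggest this for symptoms only. The HDL reduction at 10 to 40 mg/m2 did not appear dose-dependent, and clinically significant laboratory changes are themselves recorded as adverse events.
- A reader might infer that results will be labelled as results of 40 mg/m2, or that these were the first 14 subjects enrolled. The protocol says neither.

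**Conclusion.** The point holds as an unexplained inconsistency with a consequence for analysis. The Summary, 4.1 and 7.2 describe a single dose; 8.3 records 2 of 14 treated subjects (14.3%) at a quarter of it; and the stated sets and groupings summarize both doses together.

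The size cannot be fixed from the protocol. It rests on f between 0 and 1, on these two being the only subjects below 40 mg/m2, and on where they fall. The pooled mean is then 93 to 100% of the 40 mg/m2 mean over 28 subjects, 86 to 100% over 14, and 71 to 100% only in a 7-subject cell that holds both. Lower symptom incidence in the pooled table than at 40 mg/m2 is possible but not demonstrated. No view is taken on which dose is right.

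**What to change.** 1. Reconcile 4.1, 7.2, 7.3 and 8.3 on the doses given in this study, and state how the two 10 mg/m2 subjects came to receive that dose.
2. Keep the all-subjects ITT and safety summaries as stated. Replacing them with a subset who started at 40 mg/m2 would demote the stated ITT set in an unmasked study whose preliminary results have been seen, and would still contain anyone who started at 40 mg/m2 and was then reduced.
3. In 11.4 and 11.5, add efficacy and adverse event summaries or listings by dose actually received. Identify the 10 mg/m2 subjects and any subject reduced under 7.3.

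The cost is an added column or listing and a few sentences, with no new data. The by-dose cells are smaller by up to 2 subjects.

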### 8.4 Reproductive Risks and Precautions

Reproductive toxicity studies have not yet been performed with QLT091001. However, QLT091001 is a retinoid and teratogenic effects have been described for this class of compounds. Therefore, subjects will be required to take appropriate precautions. The risk of potential teratogenicity is reduced in this study given the short treatment exposure period. The risk of teratogenicity will be managed similar to the principles in the risk management programs for other oral retinoids (Accutane/Roaccutane® or Soriatane/Neotigason®), as appropriate for this study.

- Girls and women of child-bearing potential must have a negative pregnancy test result prior to being enrolled into the study. Refer to [Section 9.4.1](#) for pregnancy testing requirements.
- The Investigator must provide age-appropriate counseling to all study subjects who may be sexually active on the risk of teratogenicity and how to prevent pregnancy. Subjects will be advised to continue precautions to prevent pregnancy for at least 2 months after completion of the study drug.

## 9 STUDY PROCEDURES

### 9.1 Schedule of Events

[Table 3](#) presents the schedule of events for the study.

**TABLE 3. Schedule of Events**

| Procedure a                                                                         | Screening     | Study Day      |                |                |                |                |   |   |                |                  |                    |                      | Study Month
2, 4, 6, 8, 10,
12 (±2 wks) |
|------------------------------------------------------------------------------------------------|---------------|----------------|----------------|----------------|----------------|----------------|---|---|----------------|------------------|--------------------|----------------------|-----------------------------------------------|
|                                                                                                | Day -21 to -3 | -2/-1          | 0              | 1              | 2              | 3              | 4 | 5 | 6              | 7/8 b | 14/15 c | 30 (±4) c |                                               |
| Informed consent                                                                               | X             |                |                |                |                |                |   |   |                |                  |                    |                      |                                               |
| Demography                                                                                     | X             |                |                |                |                |                |   |   |                |                  |                    |                      |                                               |
| Inclusion/Exclusion Criteria                                                                   | X             | X              |                |                |                |                |   |   |                |                  |                    |                      |                                               |
| Medical history                                                                                | X             |                |                |                |                |                |   |   |                |                  |                    |                      |                                               |
| Complete physical exam                                                                         | X             |                |                |                |                |                |   |   |                |                  |                    |                      |                                               |
| OCT Spectralis and FAF d                                                            | X             |                |                |                |                |                |   |   |                | X                |                    | X                    | X e                                |
| Symptom-directed history and physical examination                                              |               | X              | X              | X              | X              | X              | X | X | X              | X                | X                  | X                    | X                                             |
| Blood sample for genetic test f                                                     | X             |                |                |                |                |                |   |   |                |                  |                    |                      |                                               |
| Pregnancy test g                                                                    | X             | X              |                |                |                |                |   |   |                |                  | X                  | X                    | X h                                |
| Concomitant medications                                                                        | X             | X              | X              | X              | X              | X              | X | X | X              | X                | X                  | X                    | X                                             |
| Chemistry, hematology, thyroid, and serum retinol tests i                           | X             | X              |                |                |                | X              |   |   |                | X                | X j     | X j       | X j                                |
| Coagulation testing                                                                            | X             | X              |                |                |                | X              |   |   |                | X                | X j     |                      |                                               |
| Urinalysis                                                                                     | X             | X              |                |                |                | X              |   |   |                | X                | X j     |                      |                                               |
| Vital signs k                                                                       | X             | X              | X              | X              | X              | X              | X | X | X              | X                | X                  |                      |                                               |
| ECG (12 lead) l                                                                     | X             | X              |                |                |                | X m |   |   |                | X                |                    |                      |                                               |
| BCVA                                                                                           | X             | X n | X n | X              |                |                |   |   |                | X                | X                  | X                    | X                                             |
| Color vision test (see Section 9.5.2 )                                         | X             | X o |                |                |                |                |   |   |                | X                | X                  | X                    | X                                             |
| Visual field testing (see Section 9.5.3 )                                      | X             | X              |                |                |                |                |   |   |                | X                | X                  | X                    | X                                             |
| Biomicroscopy                                                                                  | X             |                |                |                |                |                |   |   |                | X                | X                  | X                    | X                                             |
| IOP and dilated fundus exam                                                                    | X             |                |                |                |                |                |   |   |                | X                | X                  | X                    | X                                             |
| Cycloplegic refraction                                                                         | X             |                |                |                |                |                |   |   |                | X p   | X p     | X p       | X p                                |
| Full-field ERG                                                                                 | X             | X              |                |                |                |                |   |   |                | X p   | X p     | X                    | X p                                |
| Dynamic pupillometry and nystagmus testing q                                        |               | X              |                |                |                |                |   |   |                | X                | X                  | X                    | X p                                |
| Subject questionnaire (selected questions from CVFQ or LLQ; see Section 9.7. ) | X             |                |                |                |                |                |   |   |                |                  | X                  | X                    | X                                             |
| PK Sample                                                                                      |               | X              | X m | X i | X m | X i |   |   | X m | X i   |                    |                      |                                               |
| Height and weight measurement                                                                  |               |                | X r |                |                |                |   |   |                |                  |                    |                      | X s                                |
| Study treatment (after dose calculation)                                                       |               |                | X t | X              | X              | X              | X | X | X              |                  |                    |                      |                                               |
| Adverse events (AEs)                                                                           |               |                | X              | X              | X              | X              | X | X | X              | X                | X                  | X                    | X                                             |
| Videotaping of treatment-related changes (see Section 9.6.4 ) p     | X             | X              |                |                |                |                |   |   |                | X                | X                  | X                    | X                                             |
| Study completion if enrolled in extension study                                                |               |                |                |                |                |                |   |   |                |                  |                    | X                    | X                                             |

a Study procedures will be recorded in the source documents and CRF except physical exam and pregnancy test results, which are only recorded in source documents.

- b Subjects who discontinue treatment prematurely should undergo all assessments scheduled for the Day 7/8 and the subject questionnaire.
- c If a subject prematurely withdraws from the study after Day 7/8, the subject should complete the procedures for Day 14/15. If a subject prematurely withdraws from the study after Day 14/15, the subject should complete the procedures for Day 30.
- d If multiple assessments are done on the same day, OCT Spectralis and FAF must be the last procedures of the day.
- e OCT Spectralis and FAF will be done at Month 2 and thereafter at the discretion of the Investigator.
- f Only if genetic testing to confirm the *LRAT* or *RPE65* mutation was not previously done by a fully accredited genotyping laboratory.
- g For women and girls of child-bearing potential, consent and Screening serum pregnancy test must be performed  $\geq 19$  days before Day -1. A serum pregnancy test will also be done on Day -1. A urine pregnancy test will be done on Day 14/15, Day 30, and Month 2. See [Section 9.4.1](#) for further details.
- h Month 2 only.
- i Blood samples collected predose on treatment days after a 12-hour overnight fast.
- j Only if clinically significant laboratory results were observed at the previous visit.
- k Includes heart rate, resting blood pressure, respiratory rate, and temperature and collected after a 3-minute resting period. Vital signs will be recorded predose and 4 hours postdose on treatment days.
- l Perform triplicate ECG recordings (3 readings in succession approximately 1 minute apart).
- m 4 hours postdose.
- n Two baseline BCVA tests will be done on separate days (Day -2, Day -1 and/or on Day 0 before treatment is given).
- o Color vision test can be done on Day -2/-1 or on Day 0 before treatment is given.
- p At the Investigator's discretion.
- q Dynamic pupillometry and nystagmus testing if appropriate instrument(s) is available.
- r Pre-dose measurement for BSA calculation for study drug dose.
- s At the last visit only: height only, measured for subjects  $\leq 19$  years of age only.
- t Dose must be calculated and study treatment prepared (see [Section 7.2](#)), before study treatment is administered.

